##### **4.2. Inclusion Criteria: the trial will include patients meeting all of the following conditions**

- Out-of-hospital cardiac arrest
- Non-traumatic etiology
- Age  $\geq 20$  years
- Treat by participating ALS teams' paramedics
- Require advanced airway management

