### **5. Sample size estimation**

The sample size estimation is based on the primary outcome of sustained ROSC. According to previous study conducted in Taipei, sustained ROSC rate was 24.4% for SGA and 30.8 % for ETI. [15]

We estimated to enroll 852 patients to detect the absolute difference of 6.4% between the SGA and ETI group to have 80% power and a two-sided  $\alpha$ -level of 0.05.

Considering the number of OHCA patients treated by the participating ALS teams in Taipei is about 300 patients annually, we expect to have adequate number of patients of the three years study period.

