### **7. Data collection:**

The data will be collected at the Utstein-style cardiac arrest registry system in Taipei, which consisted of the following items: patient demographics (age and sex); arrest characteristics (witness status, bystander CPR), locations (public or non-public), records on automated external defibrillator (shockable or non-shockable, chest compression fraction); out-of-hospital treatment, including airway types and medication used; patient records from the EMS receiving hospitals; patient outcomes (out-of-hospital return of spontaneous circulation, sustained return of spontaneous circulation [ $\geq 2$  hours], neurologic status at discharge), and time factors (response time, scene time, transport time, call to airway time [defined as the gap between the call of the dispatch center and advanced airway insertion completion]).

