## **9. Analytic plan**

The statistical analysis methods include descriptive analysis, T-test, Chi-squared test, logistic regression, and propensity score analysis.

For the effect of airway management devices between ETI and SGA, odds ratios and 95% confidence intervals will be calculated. All tests are two-sided, and a p-value  $< 0.05$ , will be considered statistically significant.

The analysis will be done according to both intention-to-treat and as-treated principles, and reported according to the CONSORT guidelines.

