### 9.3. Subgroup analysis

Several subgroups will be analyzed to explore the association of different airway management devices, including patient's age, presenting shockable rhythm, arrest in a public location, arrest witnessed, and time of call to airway. The median will be chosen for analyzing for the call to airway time and the age of patients.

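### Splitting age at the sample median weakens the exploratory age subgroup analysis; a continuous allocation-by-age term would be a cheap improvement

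*Protocol*

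**What the plan says.** Protocol section 9.3 introduces the subgroups in exploratory terms: "Several subgroups will be analyzed to explore the association of different airway management devices, including patient's age". Age is one of five factors. For the two that are not naturally binary, the section fixes the rule: "The median will be chosen for analyzing for the call to airway time and the age of patients". No numeric age, no outside source for the median and no continuous-age analysis is given, so the natural reading is the median of the patients enrolled.

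Two other places bear on the choice. Section 7 collects "patient demographics (age and sex") for each patient, and a median can only be computed from individual ages, so the continuous values will be at hand. Section 9 already names a suitable model: "The statistical analysis methods include descriptive analysis, T-test, Chi-squared test, logistic regression, and propensity score analysis".

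**The concern.** A median split treats two patients a year apart on either side of the cut as different, and two patients decades apart on the same side as alike. If the relative effect of endotracheal intubation (ETI) and supraglottic airway (SGA) drifts with age, much of the signal lies in those within-half differences, and the split throws them away.

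Tests of effect modification have little power in a trial of this size, so a further loss matters to anyone hoping to learn about age. There is also a smaller cost in interpretation: the cut is known only once enrolment ends and need not coincide with the cut used in another trial. What is at stake is the sensitivity and readability of one exploratory analysis. The primary comparison of sustained return of spontaneous circulation does not depend on it.

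**Working it through.** **Plan's own figure.** The protocol states no power or sample size for the subgroup analysis, so there is nothing to reproduce on this point. The total of 852 in section 5 ("We estimated to enroll 852 patients to detect the absolute difference of 6.4% between the SGA and ETI group") is used below only as the planned number of patients. Whether 852 follows from the stated rates and power is a separate matter, and the argument here does not rest on it.

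**Inputs from the protocol**
- 852 patients (section 5).
- Planned rates (section 5): "sustained ROSC rate was 24.4% for SGA and 30.8 % for ETI". The log odds ratio is ln(0.308/0.692) − ln(0.244/0.756) = −0.809 + 1.131 = 0.32.
- Two-sided 0.05 level (sections 5 and 9).
- Balanced case numbers as the aim (section 4.5), taken as 1:1.
- Lowest eligible age 20 (section 4.2).

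**Assumed, because the protocol does not give them**
- The shape of the age distribution.
- How the effect changes with age.

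**Step 1: information kept.** If the effect changes linearly with age and allocation is unrelated to age, the efficiency of the split relative to a linear term is the squared correlation between age and its above-median indicator. For a normal variable this is 2/π = 0.637.

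| Assumed age distribution | Information kept | Information lost |
|---|---|---|
| Normal | 0.637 | 36% |
| Normal, mean 70, SD 16, cut off at 20 and 105 | 0.653 | 35% |
| Left-skewed | 0.636 | 36% |
| Uniform | 0.750 | 25% |

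In the normal case, 852 patients analysed with the split are worth 852 × 0.637 ≈ 542 analysed with continuous age. In the uniform case the figure is 852 × 0.75 = 639. These are not strict bounds: two right-skewed shapes that were also tried lost more (41% for a gamma with shape 4, 48% for a log-normal with log-SD 0.5). They are left out of the main range on the assumption that adult cardiac-arrest ages do not have a long upper tail.

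**Step 2: power at 852 patients.** The logistic allocation-by-age interaction was simulated with 1,500 runs per setting. The settings were the truncated normal age above, an SGA-arm rate of 24.4% and treatment log odds ratio of 0.322 at the mean age, and a prognostic age slope of −0.2 per SD.

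| True pattern | Continuous age | Median split |
|---|---|---|
| No interaction (type I error) | 4.7% | 4.9% |
| Linear, 0.25 per SD | 38% | 26% |
| Linear, 0.45 per SD | 81% | 65% |
| Step exactly at the median, ±0.3 | 36% | 50% |

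A check of the second row against step 1: 37.5% power corresponds to a standardised effect of 1.96 − 0.32 = 1.64. Multiplying by √0.653 = 0.808 gives 1.33, and Φ(1.33 − 1.96) ≈ 0.26, which agrees with the simulation.

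**Step 3: how realistic the interactions are.** The planned overall effect is 0.32. An interaction of 0.45 per SD exceeds that whole effect, so the 81% against 65% comparison is not a fair picture of this trial. An interaction of 0.25 per SD is still about 78% of it (0.25/0.32) and is the more sensible case to quote.

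The simulation allocates patients individually and ignores the cluster-crossover design. The absolute powers are therefore approximate; the comparison between the two analyses is the useful result.

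**The case against.** The strongest reply is that nothing here is stated wrongly. The analysis is exploratory, and no confirmatory claim, stopping rule or sample size rests on it. A median split is a familiar way to get two equal strata. The protocol does not call the split its only age analysis, and section 9.3 names no interaction test, so the SAP, which is not shown, may define one. At a realistic interaction the trial would probably miss it either way (38% or 26%). All of this stands, and it is why the severity is low. It does not remove the point: the median rule is written into the protocol, and a more efficient analysis is available from the same data and model.

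Three stronger readings are tempting, and the documents do not support them.
- A reader might infer that the split discards a third of the information as a matter of fact. That needs an age distribution the protocol does not give and a roughly linear change in effect. For a step exactly at the median the ranking reverses (50% with the split, 36% with a linear term).
- A reader might infer that a cut set by the data invites a favourable choice or false positives. The rule is fixed in advance and depends on ages, not outcomes. Simulated type I error stays near 5%, and age is a baseline variable, so the split biases nothing.
- A reader might infer that the result cannot be set beside other trials. The observed median can be reported with its strata, so comparison is harder but still possible.

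The same sentence of section 9.3 also covers call-to-airway time, which section 7 measures up to completed airway insertion and so after allocation. That is a different question and is not part of this point.

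**Conclusion.** The point holds as a cheap improvement of low severity. Under a roughly linear change of effect with age, the median split loses about 25% (uniform age) to 36% (normal age) of the information on effect modification. With 852 patients and an interaction of 0.25 in log odds ratio per SD, that is about 38% power against 26%. Both figures rest on an assumed age distribution and a linear change, and the power figures also assume individual allocation. There is no loss if the effect steps exactly at the median. The cost is in sensitivity and ease of comparison. Validity is not affected, and neither the primary analysis nor the trial's main conclusion changes.

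**What to change.** In section 9.3, or in the SAP with a cross-reference, base inference for the age subgroup on an allocation-by-age interaction in the planned logistic regression, with age continuous. State in advance whether the term is linear or a spline, and fix the knots if it is a spline. A spline also guards against a change that is not linear. Show the estimated ETI versus SGA odds ratio with its confidence interval at a few ages chosen beforehand. If a two-row entry is wanted for the forest plot, split at an age named in advance and label it as display only.

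The cost is about one sentence of text, one extra plot and the need to commit to a functional form. No new data or patients are needed.
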